## Abstract

**Background:**

Adverse effects such as fatigue, pain, erythema, nausea and vomiting are commonly known in patients undergoing irradiation (RT) alone or in combination with chemotherapy (RCHT). Patients suffering from these symptoms are limited in their daily life and their quality of life (QOL) is often reduced. As addressed in several trials, acupuncture can cause amelioration of these specific disorders. Especially for pain symptoms, several groups have shown efficacy of acupuncture. To what extent the difference between traditional acupuncture (*verum* acupuncture) and false acupuncture (*sham* acupuncture) is in reducing side effects and improvement of QOL is not clear.

**Methods/design:**

ROSETTA is a prospective randomized phase II trial (version 1.0) to examine the efficacy of traditional acupuncture in patients with RT-related side effects. In the experimental (*verum*) arm (n = 37) an experienced acupuncture-trained person will treat dedicated acupuncture points. In the control (*sham*) arm (n = 37) sham acupuncture will be performed to provide a blinded comparison of results.

**Discussion:**

This is the first randomized prospective trial to evaluate the effect of traditional acupuncture on RT-related side effects such as fatigue and QOL.

**Trial registration:**

ClinicalTrials.gov, NCT02674646. Registered on 8 December 2015.

**Electronic supplementary material:**

The online version of this article (doi:10.1186/s13063-017-2139-5) contains supplementary material, which is available to authorized users.

## Background

Radiation therapy (RT) is a main pillar in cancer care offering curative treatment in several indications. However, RT-related side effects develop depending on the site treated (e.g. head and neck or prostate etc.), and on individual patients’ predisposition or other factors. One of the main symptoms related to cancer treatment is the development of fatigue, which can evolve during RT and commonly persists some time after completion of treatment. Other side effects, depending on the region treated, include headache, nausea/vomiting, gastrointestinal discomfort, dysuria and others. Fatigue and subsequently a reduction in overall quality of life (QOL) is a main discomforting factor for patients treated with RT; in many patients fatigue is the only side effect observed during RT. Commonly, this leads to a reduction of daily activity and motivation, and can result in severe unhappiness and/or depression. Thus, methods for amelioration of symptoms and especially any possibilities to reduce fatigue and increase QOL are important factors for patients in the oncology setting.

Several means of supportive care to ameliorate patients’ RT-related side effects are described. In general, it has been shown that moderate exercise can improve QOL and reduce fatigue during and after treatment; additionally, light to moderate exercise can lead to improvement in oncological outcome [1, 2]. Other complementary treatments including selenium, mistletoe or several vitamins are controversial due to limited data on significant benefit; depending on the substances’ mechanisms of action, the risk of RT-related side effects may be increased. Complementary medicine such as traditional Chinese medicine (TCM) or other naturopathy concepts are consistently in discussion and are offered by many practitioners on a case-by-case basis.

For acupuncture, which is on pillar amongst others within the TCM concept, there are some data from randomized studies on back pain, headaches and other non-cancer diseases [3–15]. A large German research consortium, the GERAC-Group, has shown that acupuncture can have a significantly beneficial effect on chronic headache, back pain and joint and bone pain due to arthrosis [16–21]. In oncology, some centers have evaluated the effect of acupuncture on RT-related side effects, such as mucositis and dysphagia, and demonstrated significant reduction of symptoms [3, 10, 22–24]. However, most studies included only a small number of patients, and have not evaluated effects on general fatigue, QOL or other RT-related symptoms.

The prospective phase II ROSETTA trial (version 1.0) will include patients with tumors treated with RT in various anatomical regions. In the experimental arm an experienced acupuncture-trained person will treat dedicated traditional acupuncture points. In the control arm control acupuncture will be performed to provide a blinded comparison of results. Sham acupuncture was developed especially for randomized controlled trials as a valid comparator; compared to a pure control arm, patients receive acupuncture with needlepoints, that have no medical function and thus do not have any proven effect on the symptoms addressed [23–29].

## Methods

### Endpoints of the study

In the ROSETTA trial the main endpoint is improvement of QOL and reduction of fatigue. Secondary endpoints are reduction of RT-related side effects such as headache, nausea and skin erythema.

### Study design

The ROSETTA trial will evaluate the effect of acupuncture as a complementary treatment parallel to RT. Acupuncture is an established and accepted treatment method, which is indicated especially for pain reduction. The plan for study is to recruit 74 patients. The total study duration is planned to be 24 months.

After inclusion into the study and baseline examination, the patient is randomized into the treatment arm. Randomization is performed under the auspices of the biometrician. The randomization process will be performed with the professional web-based patient randomization service, e.g. at www.randomizer.at. The investigator or an authorized member of the study team will perform data documentation and evaluation.

Depending on the treatment arm either *verum* or *sham* acupuncture will be applied [23, 24, 26, 28, 30, 31]. Acupuncture will be performed after treatment bi-weekly during the first week of RT, thereafter weekly until the end of RT. Treatment time in both arms is identical and lies between 20 and 30 minutes. Every patient will be treated according to the treatment arm. Standardized acupuncture needles (sterile needles, e.g. 0.24 × 40 mm) will be used for both treatment types. *Verum* acupuncture is based on foraminology, the ancient Chinese knowledge of acupuncture points [32]. Control acupuncture is performed on unspecific points with no specific effect according to foraminology.

Patients will receive standardized questionnaires (European Organization for Research and Treatment of Cancer (EORTC) QLQ C-30) before their first, after their fourth and after their last acupuncture treatment. Patients will be questioned by the investigator about their feelings and symptoms and detailed information about their illness. The answers will be documented according to the standardized scoring system (Common Toxicity Criteria for Adverse Events (CTCAE)). The schedule of enrollment, interventions and assessments in the ROSETTA trial is depicted in Fig. 1.

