### Follow-up examinations during study treatment

After every acupuncture treatment, an examination will be performed. This examination includes:clinical examination according to the regulation of TCMascertainment of QOLquestionnaire on fatiguedocumentation of any symptoms and sequelae

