### Follow up

The final study visit will be 6 weeks after treatment to assess the primary endpoints. After the first 6 weeks, patients will be included into a regular follow-up schedule according to their primary disease and follow-up requirements.

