### General criteria for patient selection

All patients treated with RT or radiochemotherapy (RCHT) can be included in the trial if fulfilling the inclusion and exclusion criteria.

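### QLQ-C30 times are tied to the fourth and last needling session although RT may be of any length, and the list omits the 6-week visit named for the primary endpoints

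*Protocol article*

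**What the plan says.** All of the following is in the protocol article.

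- **Study design** sets the QLQ-C30 times: "before their first, after their fourth and after their last acupuncture treatment". The same section sets the needling schedule: "bi-weekly during the first week of RT, thereafter weekly until the end of RT".
- **General criteria for patient selection** is broad: "All patients treated with RT or radiochemotherapy (RCHT) can be included in the trial if fulfilling the inclusion and exclusion criteria". The inclusion criteria require radiotherapy without a duration or number of fractions, and no exclusion criterion concerns course length. The Background says that the trial "will include patients with tumors treated with RT in various anatomical regions", so more than one RT regimen is to be expected.
- **Follow-up examinations during study treatment** has a different timetable: "After every acupuncture treatment, an examination will be performed". Its contents include QOL and a fatigue questionnaire; the QOL instrument is not named there.
- **Follow up** adds a third timetable: "The final study visit will be 6 weeks after treatment to assess the primary endpoints".
- **Statistical considerations** makes QOL the primary endpoint, compared between two groups of 37 by the Wilcoxon test. It does not say at which time.

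**The concern.** Two of the three listed times for the primary instrument are defined by how many needling sessions a patient has, not by where the patient stands in RT. Since RT of any length qualifies, the middle time may not exist for an eligible patient, or may be the same as the last.

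The last time depends on two different things. One is planned RT length, which is normally known before randomisation. The other is whether the patient keeps attending, which is known only afterwards. A patient who gives up needling while RT continues completes the last-session form before RT ends, and no later on-treatment form is specified.

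The stage of RT matters to the outcome: the Background says that fatigue can develop over the course of RT and often persists after it. Scores taken at an earlier stage are therefore not comparable with scores taken at the end. If the arms differed in stopping, the comparison would be affected by a post-randomisation event.

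Finally, the visit named for the primary endpoints does not appear among the QLQ-C30 times, so a site following Study design to the letter would not collect the primary instrument there.

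**Working it through.** **The plan's own figure.** The sample size is not in dispute. Inputs from Statistical considerations: two-sided α = 5%, power 80%, P(x < y) = 0.69, equal groups. Noether's formula for the Wilcoxon test, with c the share of patients in one group, is

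N = (z₀.₉₇₅ + z₀.₈₀)² / [12 c (1 − c)(p − 0.5)²], c = 0.5, p = 0.69.

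This gives N = 72.5, so 37 per group and 74 in total, as stated. Power at 74 is 80.8%.

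**Session count.** Input: the needling schedule in Study design, with bi-weekly in the first week read as two sessions. For W weeks of RT, sessions = 2 + (W − 1) = W + 1.

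| RT weeks | Sessions | Fourth session | Distinct QLQ-C30 times |
|---|---|---|---|
| 1 | 2 | none | 2 |
| 2 | 3 | none | 2 |
| 3 | 4 | is the last | 2 |
| 4 | 5 | distinct | 3 |
| 5 | 6 | distinct | 3 |
| 6 | 7 | distinct | 3 |
| 7 | 8 | distinct | 3 |

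The fourth session falls in RT week 3 (2 + 1 + 1). Three distinct times need at least 4 weeks of RT. If the first week held only one session, the count would be W and each threshold would move up by one week, so the two-session reading is the more favourable to the plan.

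**Timing of the last-session form.** If every session is attended, it falls in week W, the end of RT. If needling stops early, it falls in the week of the last session received.

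**Size, under assumed shares.** The article gives no RT durations, so the share of patients without a fourth session is unknown. If 10% had none, 0.10 × 74 = 7.4 patients would lack that form. Noether power for a two-group comparison at that time, with the planned effect, would be:

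| Assumed share without the form | Patients left | Power |
|---|---|---|
| 0% | 74 | 80.8% |
| 10% | 66.6 | 76.6% |
| 20% | 59.2 | 71.6% |
| 30% | 51.8 | 65.9% |

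These rows illustrate a fourth-session comparison only. The article does not state such an analysis.

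**The three timetables side by side.** Study design: first, fourth and last session. Follow-up examinations: every session. Follow up: 6 weeks after treatment, for the primary endpoints. The first two are triggered by needling after baseline, so both end when needling ends. The third is the only one placed after treatment, and the QLQ-C30 is not listed for it.

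**The case against.** The strongest case on the other side has five parts.

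- *Frequency is undocumented.* A reader might infer that some patients in this trial will have no fourth session. The article does not support that: it shows only that eligible patients can have none. This stands.
- *Course length is not a source of bias.* A reader might also infer that the spread of the last session, from RT week 1 to week 7 or later, biases the comparison. It does not. Planned length is a baseline characteristic that randomisation balances on average, so it adds noise. Only early stopping or missed sessions come after randomisation, and they bias the result only if they differ by arm. Nothing in the article suggests that they will: both arms are needled, for the same session time, under a sham control intended to blind. This stands.
- *The primary analysis may be untouched.* If it uses the 6-week visit, the fourth-session and last-session times do not drive it. This stands as a possibility, but the QLQ-C30 list in Study design omits that visit.
- *QOL is ascertained after every session.* This does not repair the gap. Those examinations are also triggered by sessions and stop with needling, and the instrument is not named.
- *Detail may lie elsewhere.* The full protocol, an analysis plan or Fig. 1, none of them shown, may settle collection after early stopping. That is possible, and silence in an article is no fault. However, the times and the eligibility are both stated here, and no figure can create a fourth session in a two-week course. Nor can an analysis plan recover a questionnaire that was not given.

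**Conclusion.** The point holds in a limited form. Followed as written, the stated QLQ-C30 times leave eligible patients with RT of 2 weeks or less without the middle form, merge two forms at 3 weeks, and let the last form drift to an earlier stage of RT in anyone who stops needling early. They also omit the visit at which the primary endpoints are said to be assessed. The three timetables must be reconciled.

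The expected effect of course length is noise and missing mid-treatment values, of unknown extent. Bias is conditional on stopping or attendance differing by arm, and its size cannot be estimated from the article. If symptoms build up during RT, the arm that stopped earlier would look better at its last session for that reason alone. The stated sample size is not affected.

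The conclusion assumes two sessions in the first RT week, and that last session means the last one received.

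**What to change.** Collect the QLQ-C30 in all randomised patients, whether or not needling continues, at three times: before the first session, at the end of RT, and at the 6-week visit already planned. State which of these times the primary Wilcoxon test uses, and bring the three timetables into line with it. Say also that the 6 weeks run from the end of RT, so that early stopping of needling cannot move the visit.

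Keep a mid-RT form only as a secondary assessment, at a fixed RT week and only for planned courses long enough to give it a time distinct from the end of RT. A fixed week applied to everyone would repeat the gap in short courses.

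No minimum RT length is needed; it would narrow a population that the article defines broadly. No course-length covariate is needed either, and one could not enter the stated Wilcoxon test. The acupuncture schedule stays as it is.

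The cost is protocol and CRF wording, one extra questionnaire at an existing visit, and follow-up for questionnaires of patients who have stopped needling.

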**Fig. 1 Fig1:**
[figure not shown]
Schedule of enrolment, interventions and assessments in the ROSETTA trial. *EORTC* European Organization for Research and Treatment of Cancer, *QOL* quality of life, *TCM* Traditional Chinese Medicine

### Group A: *verum* acupuncture

Needlepoints

Bilateral PC 6, S 36, L 8, L 9

Unilateral R 4, R 6

### Group B: control acupuncture

Needlepoints

Four needles in the medio-axillary line below the 6th rib, bilateral

Two needles unilateral

### Baseline examination

After informed consent and inclusion into the study protocol, a baseline examination will be performed. This examination is to be performed within 2 days before initiation of study treatment and includes:complete medical history including concomitant treatmentsclinical examination according to the regulation of TCMascertainment of QOLquestionnaire on fatiguedocumentation of any symptoms and sequelae prior to radiotherapy

### Follow-up examinations during study treatment

After every acupuncture treatment, an examination will be performed. This examination includes:clinical examination according to the regulation of TCMascertainment of QOLquestionnaire on fatiguedocumentation of any symptoms and sequelae

### Follow up

The final study visit will be 6 weeks after treatment to assess the primary endpoints. After the first 6 weeks, patients will be included into a regular follow-up schedule according to their primary disease and follow-up requirements.

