### Statistical considerations

The study is powered to show that continuous acupuncture during RT can have a positive effect on QOL. ROSETTA is a prospective randomized trial comparing traditional (*verum*) acupuncture to control (*sham*) acupuncture. Randomization will be performed using automated information technology (IT)-based randomization, and patients will be allocated to groups by the Study Center within the Department of Radiation Oncology, Technische Universität München (TUM). Additionally, the study will evaluate whether acupuncture can reduce QOL-related side effects such as fatigue, headache, nausea etc.

All patient data on symptoms, side effects and QOL according to the QOL questionnaires will be documented in our dedicated study database. Evaluation of the primary endpoint (QOL) will be performed using the Wilcoxon test (*U* test) and the evaluation tool provided by the EORTC. The secondary endpoints (fatigue, headache, nausea etc.) will be evaluated using comparable statistical calculations. The interpretation of the data will be purely descriptive.

The sample size calculation is based on the Wilcoxon test and the primary endpoint. A sample size of 37 patients per group (i.e. 74 patients in total) is associated with power of 80% to detect a difference between the two groups (with two-sided α = 5%) using the Wilcoxon test, with a probability of 69% that an increase in QOL can be achieved when comparing the two groups 8 (d.h. P(x < y).

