### Data management

In the ROSETTA trial the EORTC QLQ-C30 will be used to document the QOL of patients during treatment. Data on side effects and symptoms during RT will be documented on dedicated case report forms (CRFs) designed for the trial and documented in the institutional database. All interventions and every other medical treatment will be recorded. The data will be collected in accordance with all Data Protection Regulations in the MiRO Database of the Department of Radiation Oncology, TUM.

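### The 6-week visit is named for the primary endpoint, but the text schedules the QLQ-C30 only up to the last acupuncture session

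*Protocol article*

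**What the plan says.** All references are to the protocol article.

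- **Follow up:** "The final study visit will be 6 weeks after treatment to assess the primary endpoints".
- **Statistical considerations:** "Evaluation of the primary endpoint (QOL) will be performed using the Wilcoxon test (*U* test) and the evaluation tool provided by the EORTC". No time point is given.
- **Endpoints of the study:** "the main endpoint is improvement of QOL and reduction of fatigue". Again there is no time point.
- **Study design:** patients complete the QLQ-C30 "before their first, after their fourth and after their last acupuncture treatment". After the first week, acupuncture is given "thereafter weekly until the end of RT". The section refers to Fig. 1 for the overall schedule.
- **Data management:** "the EORTC QLQ-C30 will be used to document the QOL of patients during treatment".
- **Status of the trial:** recruitment was under way when the article was submitted.

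**The concern.** A visit that exists to assess the primary endpoint should carry the instrument that measures it. In the text it does not: the listed QLQ-C30 administrations stop with the acupuncture course, and the visit comes weeks later.

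Two things are at stake. The first is data. Staff who work from Study design would not hand out the questionnaire at 6 weeks, and a patient's QOL at that time cannot be reconstructed later. The second is the question being answered. A score around the end of radiotherapy (RT) reflects acute toxicity, while a score 6 weeks later reflects recovery. The article's Background itself says that fatigue can develop during RT and commonly lasts for some time afterwards, so the two comparisons need not agree.

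**Working it through.** **Step 1. Which instrument measures the primary endpoint?** Statistical considerations names QOL and the EORTC tool. The only EORTC questionnaire named in the article is the QLQ-C30.

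**Step 2. Set the stated time points side by side.**

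| Time point | QLQ-C30 listed in the text? | Named for the primary endpoint? |
|---|---|---|
| Before first acupuncture | Yes (Study design) | No |
| After fourth acupuncture | Yes (Study design) | No |
| After last acupuncture | Yes (Study design) | No |
| 6 weeks after treatment | No | Yes (Follow up) |

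The two columns do not overlap. Data management, which places the QLQ-C30 during treatment, agrees with the first three rows and not with the fourth.

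**Step 3. How large is the gap?** Follow up does not say whether treatment means RT or acupuncture.

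- Counted from the last acupuncture, the gap between the last listed QLQ-C30 and the visit is 6 weeks.
- Counted from the end of RT: sessions are weekly until RT ends, so the last session should fall at most about 1 week before the end of RT. The gap is then at most about 6 + 1 = 7 weeks.

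The two time points stay clearly separate on either reading.

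**Step 4. Does the sample size settle the time point?** The plan states: "A sample size of 37 patients per group (i.e. 74 patients in total) is associated with power of 80" per cent, with two-sided α = 5% and P(x < y) = 0.69. Noether's formula for the Wilcoxon test with equal groups gives

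N = (z₀.₉₇₅ + z₀.₈₀)² / [12 × 0.25 × (0.69 − 0.5)²] = (1.960 + 0.842)² / (3 × 0.0361) = 7.849 / 0.1083 = 72.47,

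which is 37 per group, 74 in total. The plan's figure reproduces. Power at N = 74 is Φ(√(3 × 74) × 0.19 − 1.960) = Φ(0.871) = 80.8%. No time point enters the formula, so the calculation neither supports nor excludes either candidate.

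**Step 5. What would missing 6-week scores cost?** This is an illustration only. The documents give no rate of missing scores, so 10%, 20% and 30% are assumptions. Patients per group are rounded down, and power is Φ(√(3N) × 0.19 − 1.960).

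| Missing at 6 weeks (assumed) | Per group | N | Power |
|---|---|---|---|
| 10% | 33 | 66 | 76% |
| 20% | 29 | 58 | 71% |
| 30% | 25 | 50 | 64% |

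If the questionnaire is not given at that visit at all, the number of usable scores there is zero.

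**The case against.** **The lists may be additive.** Study design does not say that the three administrations are the only ones. One can read it as the on-treatment schedule, with Follow up adding a final visit at which QOL is measured again; the Data management sentence is not a visit schedule. Fig. 1 is the schedule of assessments, its legend mentions EORTC and QOL, and it may list a 6-week questionnaire. This is a fair reading and may be what was intended. It limits the claim: a reader might infer that the primary analysis at 6 weeks cannot be run, and the documents do not establish that. What stands is that no sentence in the text puts the QLQ-C30 at the visit named for the primary endpoint. If Fig. 1 does so, Study design and Data management are incomplete and still need correcting.

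**The per-session examinations.** The section on examinations during study treatment says "After every acupuncture treatment, an examination will be performed", and that examination includes QOL and a fatigue questionnaire. A reader might take this as a third, conflicting schedule. It does not name the QLQ-C30, and a brief check at each session can sit beside the full instrument at three points. It also ends with the last session, so it does not fill the 6-week gap.

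**Multiplicity.** A reader might infer that several time points would each be tested at 5%, with an inflated error rate. The article proposes no such procedure and says that interpretation will be descriptive.

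**Left to the analysis plan.** Which score or change score enters the Wilcoxon test is often specified there, so the silence of Statistical considerations is not itself a fault. An analysis plan can choose among collected scores, however; it cannot supply one that was never scheduled.

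**Descriptive, phase II.** This lowers the inferential stakes. A descriptive primary result still needs a defined time point with data at it, and the trial is sized at 80% power on this endpoint.

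**Conclusion.** The concern holds as an inconsistency in the text. The primary endpoint is assigned to a visit 6 weeks after treatment, while its instrument is listed at three points that all lie at or before the last acupuncture session, about 6 to 7 weeks earlier.

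The consequence depends on Fig. 1 and on actual practice. If neither adds a 6-week QLQ-C30, the visit yields no primary-endpoint score for any patient. If either does, the problem is one of wording, although it still leaves readers unable to tell from the text which score is primary. The sample size arithmetic is correct and unaffected.

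The conclusion assumes that the EORTC tool in Statistical considerations is the QLQ-C30, and that acupuncture and RT end at about the same time, as the weekly schedule implies.

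**What to change.** First check Fig. 1 and the case report forms to see whether the QLQ-C30 is already given at 6 weeks. Then name one primary time point, chosen without looking at outcomes by arm, and state it in the same way in Endpoints of the study, Study design, Follow up, Statistical considerations and Data management. Either:

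- **(a) 6-week visit as primary.** Add the QLQ-C30 at that visit to Study design, widen the Data management sentence, and say whether the 6 weeks run from the end of RT or from the last acupuncture.
- **(b) Last acupuncture session as primary** (about the end of RT). Remove from Follow up the statement that the 6-week visit is for the primary endpoints.

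Report the other time points as secondary.

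**Cost.** Option (b) is wording only and uses scores that the stated schedule already collects, but it gives up the recovery question as primary. Option (a) adds one questionnaire already in use to a visit already planned. If it has not been given there so far, patients already past the visit may lack the score, because recruitment is ongoing. The number affected should be counted and reported before (a) is chosen.
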